## **4.2 Healthy Subjects**

### **4.2.1 Inclusion Criteria**

Subjects must satisfy all of the following criteria to be enrolled in the study:

1. Must have signed an informed consent indicating that they understand the purpose of and procedures required for the study and are willing to participate in the study.
2. Be willing and able to adhere to the study visit schedule and other protocol requirements.
3. Be between 18 and 55 years of age, inclusive, at informed consent.
4. Have no clinically significant abnormalities as determined by medical history, physical examination, blood chemistry assessments, hematologic assessments including complete blood count (CBC), urinalysis (see [Attachment 2](#) for clinical laboratory analyses), measurement of vital signs, and ECG.
5. Have a body mass index (BMI) of  $\leq 32 \text{ kg/m}^2$ .
6. Must be able to produce an adequate induced sputum sample at screening, defined as a selected plug weight of at least 50 mg and a squamous cell count of  $< 20\%$  (see Study Reference Manual).

7. Must be judged by the Principal Investigator (PI) to be a subject suitable to undergo bronchoscopy.
8. Have no history of chronic respiratory disease including asthma.
9. Have no history of allergic symptoms eg, allergic rhinitis, eczema.
10. Be a non-smoker for  $\geq 1$  year at initial screening visit and have  $\leq 10$  pack-year history of smoking.
11. No other acute illness in the 6 weeks prior to screening.
12. No contraindications to the procedures in this study including clinical or research bronchoscopy.
13. No bleeding disorder including use of anticoagulants and antiplatelet agents that could place the subjects at risk for bleeding. Able to abstain from aspirin and use for 7 days and NSAID use for 3 days prior to bronchoscopy without risk.
14. No contraindications to conscious sedation or medications used in the bronchoscopy procedure.
15. To participate in the optional genomic component of this study, subjects must have signed the informed consent for genomic research indicating willingness to participate in the genomic component of the study. Refusal to give consent for this component does not exclude a subject from participation in the study.

#### **4.2.2 Exclusion Criteria**

Subjects who meet any of the following criteria will be excluded from participating in the study:

1. Be considered, in the opinion of the investigator, to be an unsuitable candidate for the study.
2. History of any clinically significant medical illness or medical disorders including (but not limited to) cardiovascular disease, neuromuscular, hematological disease including bleeding disorders, respiratory disease, hepatic or gastrointestinal (GI) disease, neurological or psychiatric disease, ophthalmological disorders, neoplastic disease, renal or urinary tract diseases, or dermatological disease.
3. Diagnosis of chronic obstructive pulmonary disease (COPD), cystic fibrosis, or other significant respiratory disorder including significant occupational or environmental exposures with ongoing respiratory symptoms.
4. Have a bronchodilator response of  $\geq 12\%$  and at least 200 mL from baseline or an FEV1 value  $< 85\%$  of predicted value at screening.
5. A known history of sleep apnea requiring medical intervention.
6. Major or traumatic surgery within the 3 months prior to screening.
7. Have a positive urine pregnancy screening result.
8. Have a recent history (within previous 6 months) of alcohol or drug abuse.

9. Positive urine toxicology screen for substances of abuse, including but not limited to amphetamines, barbiturates, benzodiazepines, cannabinoids, cocaine, methadone, opiates and tricyclic antidepressants.
10. Have a positive urine screen for nicotine (urine cotinine test).
11. Have a positive breath test for alcohol at initial screening visit.
12. Have a positive serology test for HIV antibodies, hepatitis B surface antigen (HBsAg), or hepatitis C virus antibody (anti-HCV) at screening.
13. Have a positive Phadiatop test.
14. Donated blood (volume  $\geq$  500 mL) within 56 days prior to screening.
15. Received an experimental antibody or biologic therapy within the 6 months prior to screening, or received any other experimental therapy or new investigational agent within 60 days or 5 half-lives (whichever is longer) of study start.
16. Be unable or unwilling to undergo multiple venipunctures because of poor tolerability or lack of easy access to veins.
17. Is an employee or employee family member of the investigator, study center, or Sponsor.
18. Any condition that, in the opinion of the investigator, would complicate or compromise the study, or the well-being of the subject.

### **4.3 Subjects with Asthma**

#### **4.3.1 Inclusion Criteria for Asthmatic Subjects**

Subjects must satisfy all of the following criteria to be enrolled in the study:

1. Must have signed an informed consent indicating that they understand the purpose of and procedures required for the study and are willing to participate in the study.
2. Be willing and able to adhere to the study visit schedule and other protocol requirements.
3. Be between 18 and 70 years of age, inclusive, at informed consent. Subjects who elect to undergo bronchoscopy must be between 18 and 55 years old, inclusive, at informed consent.
4. Have no clinically significant abnormalities as determined by medical history, physical examination, blood chemistry assessments, hematologic assessments including CBC, urinalysis (see [Attachment 2](#) for clinical laboratory analyses), measurement of vital signs, and ECG.
5. Have a BMI  $\leq$  32 kg/m^2.
6. Must be able to produce an adequate induced sputum sample at screening, defined as a selected plug weight of at least 50 mg and a squamous cell count of  $<$  20% (see Study Reference Manual).

7. Be a non-smoker for  $\geq 1$  year prior to screening and have  $\leq 10$  pack- year history of smoking.
8. No contraindications to the procedures in this study.
9. Symptoms compatible with asthma for at least 6 months prior to screening (wheezing, dyspnea, chest tightness), PI confirmation of diagnosis of asthma of any severity and exclusion of alternative diagnoses, and at least 1 one the following, tested sequentially at screening or based on historical documentation:
  - Bronchodilator reversibility after inhalation of SABA at screening or documented within the previous 24 months defined as an increase in  $FEV_1 \geq 12\%$  and at least 200 mL from baseline. If reversibility is  $< 12\%$  and per the opinion of the PI, a repeat bronchodilator reversibility test is performed; this result may be used for subject enrollment.
  - PC20 methacholine  $\leq 16$  mg/mL at screening or documented within 24 months prior to screening. If the PC20 is  $> 16$  mg/mL, the subject is ineligible.
  - Obstructive physiology defined as a  $FEV_1/FVC$  ratio  $< 0.7$ .
10. Fall into 1 of the categories for asthma severity (mild, moderate, or severe) as described in the study population (see Section 4.1).
11. Prebronchodilator  $FEV_1 \geq 50\%$  predicted at screening.
12. Must have clinically stable asthma (see Section 7.2.2) for at least 6 weeks prior to screening.
13. No acute illness including asthma exacerbation requiring augmentation of therapy in the 6 weeks prior to screening.
14. Have been on their current asthma controller therapy for at least 6 weeks prior to screening. Mild asthmatics must have been off asthma controller therapy for at least 6 weeks prior to screening. **Addition or withdrawal of asthma controller medications in order to be considered for participation in the study is prohibited.**
15. For asthmatic subjects participating in bronchoscopy:
  - Must be between 18 and 55 years of age, inclusive, at informed consent.
  - Must be judged by the PI to be a subject suitable to undergo bronchoscopy.
  - No lifetime medical history of life-threatening asthma including intubation and ICU admission.
  - Post-bronchodilator  $FEV_1 \geq 60\%$  predicted at screening.
  - No history of adverse events associated with a prior bronchoscopy, including but not limited to, significant worsening of asthma, significant bleeding or reaction to sedative agents.
  - No history of bleeding disorder including use of anticoagulants and antiplatelet agents that could place the subjects at risk of bleeding. Able to abstain from aspirin use for 7 days prior to bronchoscopy without risk.

- No contraindications to conscious sedation or medications used in the bronchoscopy procedure.
16. To participate in the optional genomic component of this study, subjects must have signed the informed consent for genomic research indicating willingness to participate in the genomic component of the study. Refusal to give consent for this component does not exclude a subject from participation in the study.

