## 5 STUDY SUBJECT ALLOCATION

Subjects will be assigned to 1 of 4 cohorts based on their current asthma status (healthy, mild, moderate, or severe asthma) according to the criteria described in Section 4.1 and [Table A.2](#). All healthy subjects and approximately 30 of the 50 subjects in each of the asthma severity classifications will undergo a bronchoscopy procedure with endobronchial biopsies and bronchial brushings. The healthy subject group will be split into 2 age ranges of 18 to 36 years of age or 37 to 55 years of age. Asthma subjects undergoing bronchoscopy must be between 18 and 55 years of age, inclusive.

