## 6 PRESTUDY AND CONCOMITANT THERAPY

All therapies administered for all subjects prior to this study must be recorded at screening.

Concomitant therapies must be recorded throughout the study beginning when the subject signs the consent form. All therapies (prescriptions or over-the-counter medications, including vitamins and herbal supplements; non-pharmacologic therapies such as electrical stimulation, acupuncture, special diets, exercise regimens) must be recorded in the concomitant therapy section of the CRF. Bronchodilators used to assess reversibility during pulmonary function testing must also be recorded in the concomitant therapy section of the CRF.

Moderate and severe asthmatic subjects are permitted to be on any asthma therapies at any time during the study. Modifications can be made to these therapies by their treating physician at any time during the study. Mild asthmatics must not be taking asthma controller medications eg, ICS at least 6 weeks prior to screening, but these medications may be started at any time during the study if the medical need arises. During the study, rescue medications, such as SABAs, are allowed. **Mild asthmatics must not have asthma controller therapies discontinued in order to fulfill inclusion/exclusion criteria for this study.**

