### **7.2.2 Bronchoscopy Visit**

A bronchoscopy and attendant procedures will be performed during this visit and should occur within 5 to 14 days after the baseline visit. Details of the bronchoscopy procedure are described in the Study Reference Manual.

Healthy subjects should meet the following criteria, or the bronchoscopy visit should be postponed until the subject can meet these prerequisites.

- No intercurrent illness in the 14 days prior to the bronchoscopy including upper respiratory tract infections, etc.
- Post-bronchodilator  $FEV_1 \geq 80\%$  predicted that has not declined by more than 10% from screening. For example, if baseline  $FEV_1$  is 3.86 liters, a decrease of  $\geq 386$  mL would render the subject ineligible for the bronchoscopy on that day.
- Healthy subjects who cannot complete the bronchoscopy visit within 14 days of the baseline visit will be given an additional 14 days to complete the procedure. If the subject could not complete the bronchoscopy after the additional 14 days they will be discontinued from the study.

Asthmatic subjects should not withhold any inhaled medications before the bronchoscopy visit. A pre- and post-bronchodilator reversibility test will be performed prior to the bronchoscopy. The postbronchodilator  $FEV_1$  from this test serves as the prebronchoscopy  $FEV_1$  baseline determining eligibility. Asthmatic subjects must meet the following criteria or the bronchoscopy visit should be postponed until the subject can meet these prerequisites.

- Must be between 18 and 55 years of age, inclusive, at informed consent.
- Clinically stable asthma for at least 14 days prior to the bronchoscopy procedure, as defined by:
  - no clinically significant worsening of asthma requiring augmentation of therapy (eg, increased use of rescue medications, antibiotics, systemic steroids, increased controller medications, hospitalization) as per judgment of the investigator,
- Post-bronchodilator  $FEV_1 \geq 60\%$  predicted that has not declined by more than 10% from screening. For example, if baseline  $FEV_1$  is 2.56 liters, a decrease of  $\geq 256$  mL would render the subject ineligible for the bronchoscopy on that day.
- No intercurrent illness in the 14 days prior to the bronchoscopy including upper respiratory tract infections etc.

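### Asthmatic subjects having bronchoscopy are not asked whether they can stop NSAIDs for 3 days, although healthy subjects having the same biopsies are

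*Protocol*

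**What the plan says.** Section 5 of the Protocol sends all healthy subjects to bronchoscopy, and "approximately 30 of the 50 subjects in each of the asthma severity classifications will undergo a bronchoscopy procedure with endobronchial biopsies and bronchial brushings".

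Each population has its own bleeding-risk criterion:

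- **Healthy subjects (Section 4.2.1, criterion 13).** No bleeding disorder and no risky anticoagulant or antiplatelet use. The subject must be able to go without aspirin for 7 days and, in addition, meet the condition "NSAID use for 3 days prior to bronchoscopy without risk".
- **Asthmatic bronchoscopy subjects (Section 4.3.1, criterion 15).** A near-identical opening on bleeding disorders, anticoagulants and antiplatelet agents, then "Able to abstain from aspirin use for 7 days prior to bronchoscopy without risk". The bullet ends there.

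The NSAID clause came in with Amendment 2, item 5. The reason given is that NSAIDs, too, can cause bleeding. The stated purpose is to let subjects taking them stop for 3 days before the procedure. Only Section 4.2.1 and the abbreviation list are shown as changed.

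For the procedure itself, Section 7.2.2 states: "Details of the bronchoscopy procedure are described in the Study Reference Manual".

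**The concern.** The two criteria serve the same purpose for the same procedure, yet one is shorter. An asthmatic who cannot safely stop an NSAID passes criterion 15 as written; a healthy subject in the same position fails criterion 13. The sponsor's bleeding rationale concerns the drug and the procedure and does not depend on whether the subject has asthma.

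The matter at stake is subject safety. Section 11.1 lists lower-airway bleeding among the complications of bronchoscopy and says that death from bleeding, though rare, can occur. The same section accepts that the procedures may bring the subjects no benefit. The point does not require asthmatics to bleed more than healthy subjects, and the protocol does not clearly say that they do.

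**Working it through.** There is no planned figure to reproduce. The check compares the texts and then counts the subjects governed by each wording.

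**1. The two criteria side by side**

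| Element | Healthy, criterion 13 | Asthmatic, criterion 15 |
|---|---|---|
| Bleeding disorder | excluded | excluded, including by history |
| Risky anticoagulant or antiplatelet use | excluded | excluded |
| Able to stop aspirin | 7 days | 7 days |
| Able to stop NSAIDs | 3 days | not mentioned |

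Both state an ability to abstain. Neither instructs anyone to stop the drug.

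**2. Is the NSAID condition set elsewhere for asthmatics?** It is absent from the rest of Section 4.3.1 and from Sections 4.3.2, 6, 7.2.2 and 7.3.3, and from Attachment 1.2 with its footnotes. The only instruction in Section 7.2.2 on asthmatics' own medication before bronchoscopy is that inhaled drugs should not be withheld. Criterion 13 is therefore the only operative NSAID statement in the current protocol.

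**3. Do the general safeguards explain the difference?** The main ones exist in both cohorts:

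- *Investigator's judgement of suitability.* Healthy criterion 7 reads "Must be judged by the Principal Investigator (PI) to be a subject suitable to undergo bronchoscopy". Asthmatic criterion 15 has an equivalent bullet.
- *No contraindications.* Healthy criterion 12 reads "No contraindications to the procedures in this study including clinical or research bronchoscopy". Asthmatic criterion 8 reads "No contraindications to the procedures in this study".
- *Investigator veto.* Exclusions 1 and 18 for healthy subjects; exclusions 1 and 19 for asthmatics.
- *Medication record.* Section 6 requires recording for everyone, from "All therapies (prescriptions or over-the-counter medications, including vitamins and herbal supplements" onwards, so NSAID use should be known to the investigator.

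Healthy subjects had these safeguards and the antiplatelet clause, and the sponsor still added the NSAID condition for them. The shared safeguards therefore do not explain why it was left out for asthmatics.

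**4. How many bronchoscopies fall under each wording?** Section 8.2 sets a ceiling of 30 bronchoscopies in each of the four subject categories.

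- Under criterion 15: 3 × 30 = 90
- Under criterion 13: 1 × 30 = 30
- Share under the shorter wording: 90 / (90 + 30) = 90/120 = 75%

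**5. How many subjects might be affected?** The documents do not say what share of asthmatics cannot stop NSAIDs for 3 days. Purely as assumptions:

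- 1%: 0.01 × 90 = 0.9, about 1 subject
- 5%: 0.05 × 90 = 4.5, so 4 to 5 subjects
- 10%: 0.10 × 90 = 9 subjects

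Each would still face the investigator's review of suitability.

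**The case against.** The best defence is that the asthmatic criteria are not simply a weaker copy of the healthy ones.

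- Criterion 15 also excludes anyone with significant bleeding at a previous bronchoscopy and covers a history of bleeding disorder; the healthy criteria word neither in that way.
- Under exclusion 2 of Section 4.3.2, asthmatics with stable comorbidity enter only after consultation with the sponsor's medical monitor. That could catch a subject who depends on an NSAID.
- Section 11.1 relies on precautions in the Study Reference Manual to reduce harm from bronchoscopy. Footnotes to Attachment 1.2 place the drug-withholding lists for reversibility and methacholine testing in that manual, so an NSAID rule may be there too.
- Amendment 2 changed the BMI limit in both populations but the NSAID clause in only one. It presents the clause as clarifying an abstention time, and makes no statement that the other safeguards were insufficient.
- The clause states an ability, so adding it would not by itself make anyone stop an NSAID.

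Much of this stands. The documents do not show whether the omission was deliberate or an oversight, and the manual could close the gap in practice. That the sponsor found the general safeguards insufficient for healthy subjects is an inference from its having added the clause; it is not stated. But none of the asthmatic safeguards mentions NSAIDs, and a previous uneventful bronchoscopy, or none at all, says nothing about current NSAID use. Medical-monitor consultation depends on the underlying condition and is not triggered by the drug. A possible rule in a separate manual does not explain why the protocol states the condition for one cohort and leaves it out for the other.

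**Conclusion.** The concern holds. The eligibility wording on bleeding risk is inconsistent between two cohorts undergoing the same procedure, no reason is given, and the sponsor's own rationale covers both. The shorter wording governs up to 90 of up to 120 bronchoscopies, taking the protocol's ceilings as the numbers performed. The number of asthmatics who could not stop an NSAID is unknown; the assumed shares of 1% to 10% give roughly 1 to 9.

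Confidence is high for the mismatch in the text. Whether a gap remains in practice depends on the Study Reference Manual. This is an inexpensive safety correction that should be made. It has no bearing on the primary objective, sample size or analysis.

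**What to change.** In Section 4.3.1, criterion 15, extend the last sentence of the bleeding-disorder bullet so that the 7-day aspirin condition is followed by "NSAID use for 3 days prior to bronchoscopy without risk", as in criterion 13 of Section 4.2.1. Check the Study Reference Manual at the same time so that it agrees for both cohorts.

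The cost is one line of protocol wording. A few asthmatics unable to stop NSAIDs for 3 days would become ineligible for bronchoscopy. Because criterion 15 applies only to bronchoscopy participants, they could still join the non-bronchoscopy part while it is open: about 50 − 30 = 20 places per severity group, or 3 × 20 = 60 in all.

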#### **4.3.2 Exclusion Criteria for Asthmatic Subjects**

1. Be considered, in the opinion of the investigator, to be an unsuitable candidate for the study.
2. History of any clinically significant medical illness or medical disorders that place the subject at risk from participation by the judgment of the PI including (but not limited to) cardiovascular disease, neuromuscular, hematological disease including bleeding disorders, respiratory disease, hepatic or GI disease, neurological or psychiatric disease, ophthalmological disorders, neoplastic disease, renal or urinary tract diseases, or dermatological disease. Subjects with stable, well-controlled conditions may be eligible after consultation with the Sponsor's medical monitor.
3. Diagnosis of allergic bronchopulmonary aspergillosis (ABPA), allergic bronchopulmonary mycosis (ABPM), or occupational asthma.
4. Diagnosis of COPD, cystic fibrosis, or other significant respiratory disorder including significant occupational or environmental exposures with ongoing respiratory symptoms.
5. If a PC20 methacholine test is performed during screening for enrollment, a PC20 result > 16 mg/mL excludes the subject from the study (refer to 4.3.1, inclusion criterion #9).
6. Major or traumatic surgery within 12 weeks of screening.
7. A known history of sleep apnea requiring medical intervention.
8. Have a positive urine pregnancy screening result.
9. Have a recent history (within previous 6 months) of alcohol or drug abuse.
10. Positive urine toxicology screen for substances of abuse, including but not limited to, cannabinoids, cocaine, and methadone.
11. Positive urine toxicology screen, including but not limited to amphetamines, barbiturates, benzodiazepines, opiates and tricyclic antidepressants, unless the results can be reliably attributed to a concomitant prescription medication by the PI for a condition identified on medical history, in which case the subject may be enrolled after consultation with and agreement of the Sponsor's medical monitor.
12. Have a positive urine screen for nicotine (urine cotinine test).
13. Have a positive breath test for alcohol at initial screening.
14. Have a positive serology test for HIV antibodies, HBsAg, or anti-HCV at screening.

15. Donated blood (volume  $\geq$  500 mL) within 56 days prior to screening.
16. Be unable or unwilling to undergo multiple venipunctures because of poor tolerability or lack of easy access to veins.
17. Received an experimental antibody or biologic therapy within the 6 months prior to screening, or received any other experimental therapy or new investigational agent within 60 days or 5 half-lives (whichever is longer) of study start.
18. Is an employee or employee family member of the investigator, study center, or Sponsor.
19. Any condition that, in the opinion of the investigator, would complicate or compromise the study, or the well-being of the subject.

